**Plantar region**				
	Solid ball massage	Slow circular movements shall be carried out with slight pressure on the sole of the foot. The stimulus should be applied below the pain threshold.	Three areas shall be worked on: near the heel, in the middle of the sole of the foot and below the metatarsal head. Circular movements shall be carried out.	5 seconds in each area, bilaterally
	Solid ball massage	Linear movements shall be carried out on the sole of the foot exerting a slight pressure from the heel to the metatarsals and from the metatarsals to the heel.	The maneuver shall include slight flexion and extension movements of the toes.	15 repetitions shall be performed for each foot
**Achilles region**				
	Foam roller	The movement shall be performed from the most distal part of the leg to the region of myotendinous connection with the calf muscles.	The exercise is to be assisted with slight plantar flexion and extension movements by the patient. The exercise can be enhanced by crossing a leg in extension over the leg subject to the work stimulus	15 slow sliding movements
**Soleus and calf muscles**				
	Foam roller	Movement assisted with slight plantar flexion and extension movements shall be performed. The roller will move over the calf muscle.	The exercise can be enhanced by crossing a leg in extension over the leg subject to the work stimulus.	15 slow sliding movements
**Extensor retinaculum of the ankle**				
	Foam roller	With the foam roller placed in the anterior region of the ankle, a sliding motion while exerting slight pressure on the anterior region of the ankle shall be performed.	Performed with the patient in a quadruped position. Slight plantar and dorsal flexion movements of the ankle can be combined.	15 slow movements
**Muscle compartment of the anteroexternal region of the leg**				
	Foam roller	Movements shall be performed on the anteroexternal region of the leg, with slight compression stimuli and longitudinal release of the tibialis anterior, toe extensor, and peroneal muscles.	Performed with the patient in a quadruped position incorporating a slight hip rotation	15 slow movements
**Hamstring region**				
	Foam roller	Bilateral work on the hamstring region using a foam roller shall be performed by rolling each hamstring on the foam roller bilaterally and attempting the widest possible run.	Performed with the patient seated in such a way that the hamstring muscles are supported on the foam roller.	10 slow movements
	Foam roller	Unilateral work on the hamstring region using a foam roller shall be performed focusing the work on one leg while making slight flexion and extension movements of the knee.	Performed with the patient seated in such a way that the hamstring muscles are supported on the foam roller.	10 slow movements
**Adductor muscles**				
	Solid ball massage	The exercise shall be carried out in 3 different areas of the inner thigh region: middle third, proximal third and distal third, starting on the distal third. The ball will be placed between the legs and slight pressure will be applied.	With sustained pressure, slow movements shall be performed with one leg so the solid ball moves in a circle. Movements shall be performed using each leg, changing the position of the ball to the medial third, and then the proximal third.	5 slow movements
**Abductor muscles**				
	Foam roller	The patient shall be positioned in lateral decubitus, with the foam roller on the side of the thigh, applying slow slides on the back of the thigh	The longitudinal run should be as wide as possible.	15 slow movements
**Pelvitrochanteric muscles**				
	Foam roller	The patient shall be seated on the foam roller, flexing a hip while placing the foot with the sole resting on the floor to ensure greater body weight on the gluteal and pelvitrochanteric region on the opposite side.	Perform smooth movements sliding the gluteal region over the foam roller. Then change legs.	15 slow movements

### Data Analysis

The distribution of the sample, the changes after the intervention and follow-up period in each group, and the intra and interindividual effect will be analyzed. We will use the intent-to-treat method to include all individuals who were randomized in the final data analysis.

The statistical analysis will be carried out using SPSS statistical software (version 19.0; IBM Corp). The Kolmogorov-Smirnov test will be used to test for normality, and the Levene test will be used to test for homoscedasticity. If the conditions of normality and homoscedasticity are violated, nonparametric tests will be used.

Descriptive statistics (mean and standard deviation) will be calculated for all dependent variables. A one-way repeated measures analysis of variance will be used to compare the groups (experimental and control) at 3 assessment times (baseline, posttreatment, and follow-up). If the interaction is found to be significant, pairwise comparisons will be performed. The significance level will be set at α=.05. To control the error rate, Bonferroni correction will be applied. The results of the *F* test will depend on the significance of Mauchly sphericity. If significant, the Greenhouse-Geisser correction will be used. To assess clinical relevance, we will calculate the standard error of measurement and minimum detectable change for each dependent variable.

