### Sample Size

The target sample size for inclusion in the study is 70 patients. The sample size is justified with respect to the prevalence of patients with congenital coagulopathies; there are 2039 patients with either hemophilia A and B or von Willebrand disease in Spain, of which 612 meet the selection criteria for the study (Spanish Federation of Hemophilia). Based on these data, the sample size at national level would be 236 individuals, with a confidence level of 95% and an expected dropout ratio of 15%. Thus, a sample size of a total of 70 patients from the 5 centers will be used.

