### Outcome Measures

Baseline assessments will be carried out at Hemophilia Association centers. Measurements will be performed by a physiotherapist who is unaware of patient group assignments.

After the treatment period and 3 months after completion, the patients included in both groups (experimental and control) will be re-evaluated by the same rater under the same conditions as their initial evaluation.

Dependent variables (range of motion, joint pain, functionality, joint state, muscle strength, muscle flexibility, and record of activity) will be measured at each study assessment (baseline, posttreatment, and follow-up). A 10-point visual analog scale will be used to evaluate patient perception of joint pain, ranging from 0 (no pain) to 10 (maximum perceived pain). An algometer (FPN100; Wagner Instruments) will be used for the assessment of pressure-induced pain (the amount of pressure at which the person perceives pain), both at the joint and at other body sites [28]. Pressure will be applied gradually at the site, increasing at rate of 50 kPa/s until the patient reports that the sensation is painful [29]. In patients with ankle arthropathy, bilateral measurements will be taken anterior to the lateral malleolus (ankle) [30] and at two other sites—the spinous process of the L5 vertebra and on the extensor carpi radialis longus muscle of the forearm (5 cm distal to the lateral epicondyle of the humerus) [28]. Using a portable instrument [31] for assessing physical activity, patient physical activity level (average number of steps per day, average distance per day, average amount of active time, and energy consumption) will be recorded. The Hemophilia Joint Health Score [32] will be used to evaluate the joint condition of knees, ankles, and elbows. It includes 8 items (inflammation and its duration, pain, atrophy and muscle strength, crepitus, and reduced flexion and extension) ranging from 0 to 20 points per joint (the higher the score, the greater the joint deterioration).

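### The plan promises an intent-to-treat analysis of everyone randomized, but the repeated measures ANOVA it names keeps only patients measured at all three visits

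*Protocol article*

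**What the plan says.** All statements are in the protocol article.

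- **Analysis set (Data Analysis):** "We will use the intent-to-treat method to include all individuals who were randomized in the final data analysis".
- **Method (Data Analysis):** "A one-way repeated measures analysis of variance will be used to compare the groups (experimental and control) at 3 assessment times". The sphericity rule follows: "The results of the *F* test will depend on the significance of Mauchly sphericity", with Greenhouse-Geisser as the correction. On software: "The statistical analysis will be carried out using SPSS statistical software (version 19.0; IBM Corp").
- **Fallback (Data Analysis):** "If the conditions of normality and homoscedasticity are violated, nonparametric tests will be used". The tests are not named.
- **Visits (Outcome Measures):** the dependent variables "will be measured at each study assessment (baseline, posttreatment, and follow-up"). The list covers mobility, pain, function, joint status, strength, flexibility and activity. Ankle bleeding, which the Abstract gives as the primary outcome, is not on it.
- **Dropout (Sample Size):** the section gives "an expected dropout ratio of 15" percent, in the sentence that arrives at a national figure of 236. The target of 70 follows in the next sentence.

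The article mentions no imputation, carry-forward or mixed model.

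**The concern.** The analysis set and the analysis method are fixed in the same section, and they cannot both hold once a patient misses a visit. Mauchly's test and the Greenhouse-Geisser correction belong to the classical repeated measures ANOVA. That analysis works on one complete row of three values per patient, and SPSS removes incomplete rows listwise. A patient measured after treatment but absent 3 months later is therefore lost from the posttreatment comparison too, although that value was collected.

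Two things are at stake. The report would describe as intent-to-treat an analysis that leaves out some randomized patients. It would also discard observed data from a small trial whose Discussion claims high statistical power. The arms carry different burdens: one performs a home roller programme for 3 months, the other keeps its usual routine. Dropout could therefore differ by arm or relate to pain or function, and a complete-case comparison would then be open to bias.

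**Working it through.** **Inputs**

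- 70 patients (Sample Size), allocated 1:1 (Abstract), so 35 per arm.
- Three assessments (Outcome Measures).
- 15% dropout (Sample Size), assumed to apply to the 70.
- α = .05 (Data Analysis), sidedness not given.

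**The plan's own figures**

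The 70 cannot be reproduced. No effect size, standard deviation, event rate or power is given, and no step leads from 236 to 70.

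The 236 matches a finite-population survey formula, n = N z² p(1−p) / [e²(N−1) + z² p(1−p)]. With N = 612 and z = 1.96, and with p = 0.5 and e = 5% assumed (neither is in the article), n = 236.2. That is before any dropout allowance: 236.2 / 0.85 = 277.9. So the 15% does not visibly enter the 236 either, and applying it to the 70 is a reading of the text rather than something the text states.

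**Patients analysed under listwise deletion**

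Complete cases = 70 × (1 − d), with d the share missing at least one visit.

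| d | Complete cases | Excluded |
|---|---|---|
| 5% (assumed) | 66.5 | 3.5 |
| 10% (assumed) | 63 | 7 |
| 15% (Sample Size) | 59.5 | 10.5 |
| 20% (assumed) | 56 | 14 |

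At 15%, about 59 to 60 patients are analysed, or 35 × 0.85 = 29.75 per arm. Ending with 70 complete cases would require 70 / 0.85 = 82.4, so 83 randomized.

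**Illustration of lost precision**

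Assume a simple two-sided comparison of two means, 80% power and equal arms. The detectable standardized difference is (1.96 + 0.84) × √(2/n).

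- n = 35 per arm: 0.67 SD.
- n = 30 per arm: 0.72 SD.
- n = 29.75 per arm: 0.73 SD.

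Power for 0.67 SD falls from 80% to about 73 to 74%. The loss is modest, and the plan sets no target against which to judge it.

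**Whether bias follows**

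Suppose experimental patients with poor posttreatment values skip the follow-up visit, and all pairs of visits are equally correlated (0.6, for illustration) with equal variances. For standardized values with no treatment effect, the expected change from baseline to follow-up given the posttreatment value y is 0.6y − 0.6y = 0, so that contrast is not shifted. The expected change from baseline to posttreatment is y − 0.6y = 0.4y, so that contrast is shifted by deleting these patients, although all their posttreatment values were observed. Whether there is bias, and how much, depends on the dropout mechanism and the contrast. The article fixes neither the mechanism nor dropout rates by arm.

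**The case against.** **Imputation may be specified elsewhere.** This is the strongest point. The article condenses a fuller protocol, handling of missing data is commonly left to an analysis plan, and multiple imputation before the ANOVA would honour the promise. This stands as a condition on the conclusion. It does not remove the point, because the article goes beyond silence: it states an analysis set and names a method that cannot deliver it without a further step.

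**The primary outcome is not shown to be affected.** This stands. Bleeding frequency is not among the variables listed for each assessment, and no model is named for it separately.

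**The nonparametric fallback might not delete patients.** This stands in part. Between-group rank tests at each visit would keep patients with posttreatment data only. Tests on complete blocks or pairs, such as Friedman or Wilcoxon signed-rank, would not. The article does not say which are meant.

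**Stronger readings the document does not support.**

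- *A loss of 28%.* A reader might apply 15% independently at each of the two later visits: 1 − 0.85² = 27.75%, or about 19 patients. The article gives one dropout ratio, and patients lost before the posttreatment visit are usually also absent at follow-up.
- *A bias of 0.10 SD in favour of the roller.* This needs 20% of the experimental arm to leave, those patients to score 0.5 SD worse than those who stay (0.20 × 0.5 = 0.10), and no comparable loss among controls. None of this is in the article. Controls might also leave for lack of benefit, which could reverse the direction. The exercises are described as short and mostly of slight pressure.

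**A mixed model does not cure dropout that depends on unobserved values.** Correct, which is why a sensitivity analysis belongs with it.

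**Conclusion.** The point holds as a conflict between a stated analysis set and a stated method. Unless an imputation step exists outside the article, the planned ANOVA yields a complete-case analysis under an intent-to-treat label for the outcomes listed in Outcome Measures. It extends to bleeding only if bleeding is analysed with the same model.

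The size is 10 to 11 of 70 patients excluded, assuming that the 15% applies to the 70 and that every dropout misses at least one visit. The conflict itself does not depend on the exact rate, since one missed visit is enough. Bias is possible if dropout differs by arm or depends on outcome. A reader might infer that the comparison must favour the roller, but the document supports neither a direction nor a size.

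**What to change.** 1. Replace the repeated measures ANOVA with a likelihood-based linear mixed model: group, visit and group-by-visit as fixed effects, unstructured covariance across the three visits, REML. Use every available visit of every randomized patient in the assigned arm. Mauchly's test and Greenhouse-Geisser are then no longer needed. Multiple imputation before the ANOVA is an acceptable alternative if the ANOVA is to be kept.
2. State the missing-at-random assumption, and add one sensitivity analysis that assigns worse outcomes to experimental-arm dropouts. Fix the amount beforehand and define worse for each outcome (for example, less ankle mobility or more pain).
3. Name the nonparametric fallback and say how it treats a missing visit.
4. If neither a mixed model nor imputation is adopted, call the analysis complete-case and report the number excluded in each arm.

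The cost is wording and a little more programming, with no new data or visits. The drawback is reliance on missing at random in the main analysis, which the sensitivity analysis probes but cannot verify. Patients with only a baseline value stay in the model but add little information on the treatment effect.

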### Randomization

Participants will be randomly assignment using opaque envelopes to one of two groups—experimental and control. Random assignment of patients will be carried out after cluster recruitment (based on hemophilia type and patient age) to ensure homogeneity of the study groups. This assignment will be carried out by a person who is not involved in the study objectives and who is unaware of the identity of the participants.

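### The named test, a one-way repeated measures ANOVA, has no group factor or interaction; the group-by-time ANOVA probably meant is valid but gives up power that a baseline-adjusted group contrast would keep

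*Protocol article*

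**What the plan says.** The efficacy model is given in Data Analysis in one sentence: "A one-way repeated measures analysis of variance will be used to compare the groups (experimental and control) at 3 assessment times". The next sentence sets the order of testing: "If the interaction is found to be significant, pairwise comparisons will be performed". The section also announces that "the intra and interindividual effect will be analyzed", sets alpha at .05, and applies Mauchly's test, the Greenhouse-Geisser correction and a Bonferroni correction.

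Under Outcome Measures, the dependent variables "will be measured at each study assessment (baseline, posttreatment, and follow-up"), so baseline is the first of the three repeated levels. No adjustment for the baseline value is mentioned. Under Randomization, assignment takes place "after cluster recruitment (based on hemophilia type and patient age) to ensure homogeneity of the study groups"; these factors do not reappear in Data Analysis.

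**The concern.** One-way describes a design with a single factor, and in a repeated measures ANOVA that factor is time. Such a model has no term for experimental versus control, and an interaction needs two factors. The sentence therefore assigns the test a job it cannot do, and the next sentence depends on a quantity it does not produce. Two analysts could run different analyses from the same text.

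Under the likely intended two-factor model, a second and smaller issue remains. The interaction spreads the treatment effect over three visits, one of them before randomization, and pairwise comparisons follow only if that 2-df test is significant. A trial of 70 patients has little power to spare.

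**Working it through.** **Inputs.** From the article: 70 patients, 1:1 allocation (35 per arm), expected dropout 15%, three visits, alpha .05 (taken as two-sided). 35 × 0.85 = 29.75, so about 30 per arm. Assumed, because the article gives none of them: unit SD, compound symmetry with correlation ρ, and the effect sizes. The article states no power or effect size for this analysis, so there is no planned figure to reproduce first.

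**Step 1: the literal test.** With all 70 patients pooled, the one-way test has a time F on 2 and 138 df. Its noncentrality is N·Σ(m_t − m̄)²/(1 − ρ), where m_t are the visit means over both arms.

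- *No treatment effect, both arms drift by 0.3 SD, ρ = 0.5.* Means are 0, 0.3, 0.3; the sum of squares is 0.06; the noncentrality is 70 × 0.06/0.5 = 8.4. The test rejects 73% of the time, and simulation also gave 73%. The group-by-time test rejected in 5.4%.
- *True 0.5 SD group effect, common change of −0.25 SD.* The pooled mean after baseline is −0.25 + 0.5/2 = 0, so the noncentrality is 0. The test rejected in 4.7% of runs, against 56% for group-by-time.

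The literal test responds to change over time, not to the difference between groups.

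**Step 2: the probable intended test.** With n per arm and group differences d_t at the three visits, the group-by-time F has noncentrality (n/2)·Σ(d_t − d̄)²/(1 − ρ) on 2 and 4(n − 1) df. For n = 30 that is 2 and 116 df.

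- *Effect 0.6 SD, halving by follow-up:* d = 0, 0.6, 0.3; the sum of squares is 0.18; noncentrality 15 × 0.18/0.5 = 5.4 (ρ = 0.5) or 15 × 0.18/0.3 = 9.0 (ρ = 0.7).
- *Effect sustained:* d = 0, 0.6, 0.6; the sum of squares is 0.24; noncentrality 7.2 or 12.0.

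**Step 3: baseline-adjusted ANCOVA at posttreatment.** SE = √[(2/n)(1 − ρ²)].

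- *ρ = 0.5:* √(0.0667 × 0.75) = 0.224, and 0.6/0.224 = 2.68.
- *ρ = 0.7:* √(0.0667 × 0.51) = 0.184, and 0.6/0.184 = 3.25.

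| Setting | ρ | Group-by-time: formula / simulated | ANCOVA: formula / simulated |
|---|---|---|---|
| Effect halves | 0.5 | 53% / 54% | 75% / 76% |
| Effect halves | 0.7 | 76% / 76% | 89% / 88% |
| Sustained | 0.5 | 66% / 68% | 75% / 75% |
| Sustained | 0.7 | 87% / 88% | 89% / 89% |

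Formula and simulation agree within about 2 points.

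**Step 4: a milder case.** With no dropout (35 per arm) and a sustained 0.5 SD effect, simulated power at ρ = 0.3, 0.5 and 0.7 was 41%, 58% and 79% for group-by-time, and 57%, 66% and 82% for ANCOVA.

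**Step 5: the balancing factors.** With a 1 SD stratum effect, balanced strata, ρ = 0.5 and a 0.5 SD treatment effect, ANCOVA power was 64.5% without the stratum term and 64.7% with it. Under no treatment effect, the group-by-time test that ignores strata rejected in 4.8%.

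**The case against.** The best defense is that this is a misnamed model, not a missing comparison. The section speaks of comparing the groups, of effects within and between individuals, and of an interaction. Together these describe a 2×3 mixed ANOVA, whose interaction compares changes from baseline and holds its type I error. That stands. The power loss is then a matter of efficiency, not validity. It depends on assumed values, and the largest figure comes from a fading effect with ANCOVA placed at the visit where the effect peaks. That also stands, which is why the sustained case is shown beside it.

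Four stronger readings are tempting, and the article does not support them.

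- *Efficacy will be judged by comparing p values within each arm.* Under a common 0.3 SD drift and no treatment effect, that would show a significant change in the experimental arm alone in about 24% of trials. The article plans to look at changes in each group, but nowhere makes such a comparison the basis for inference.
- *Baseline is ignored.* It is a level of the time factor and enters through the interaction.
- *The two ankles of each patient will be counted as independent.* Arthropathy must be bilateral and several measures are taken on both sides, but the article does not say how they enter the model. The 11% type I error that follows from independence at an assumed correlation of 0.5 describes an analysis nobody has stated.
- *Omitting hemophilia type, age and center is an error.* A condensed article may leave covariates to a fuller document, and omitting strata did no harm in the check above.

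**Conclusion.** The point holds in two parts of unequal weight. First, the test as named cannot deliver the group comparison or the interaction that the plan relies on. This follows from the text alone, needs no assumptions, and must be corrected. Second, if the intended model is the 2×3 mixed ANOVA, the analysis is valid but less powerful than a baseline-adjusted group contrast. In simulation the gap runs from about 1 percentage point (sustained effect, ρ = 0.7) to about 22 points (effect halving by follow-up, ρ = 0.5), assuming 30 per arm, a 0.6 SD effect and compound symmetry. A reader might infer that the trial plans no between-group test at all; the surrounding wording speaks against that. The finding concerns the continuous secondary outcomes. Ankle bleeding frequency, which the Abstract names as primary, needs its own model and is not addressed here.

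**What to change.** In Data Analysis, replace the one-way repeated measures ANOVA with wording such as: *For each continuous secondary outcome, the posttreatment and follow-up values will be analyzed in a linear mixed model with group, visit, group-by-visit and the baseline value as fixed effects and patient as random effect. The main contrast is the adjusted group difference at posttreatment; the difference at follow-up will also be reported. Both will be given with 95% confidence intervals, whether or not an interaction test is significant.*

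Add one sentence for ankle-level measures: use the patient as the unit (mean of the two ankles), or nest ankle within patient. Adjustment for hemophilia type and age is optional.

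The cost is a protocol wording change, made before the data are analyzed, and a few degrees of freedom. No measurements beyond those planned are needed, and the mixed-model procedure in SPSS version 19 can fit the model.

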**Methods:**

Patients with ankle arthropathy (N=70) will be recruited, enrolled, and assigned to one of two groups—experimental or control—in a 1:1 allocation ratio. Patients will be recruited from 5 centers in different regions of Spain. Patient data will be collected at baseline, posttreatment, and follow-up. The primary outcome will be frequency of ankle joint bleeding (self-reported). The secondary outcomes will be ankle range of motion (measured with a digital goniometer); joint pain (measured with a visual analog scale and an algometer); joint status (measured using the Hemophilia Joint Health Score); muscle strength (measured with a dynamometer); functionality of lower limbs (measured using the 6-minute walking test); activity (self-reported); and muscle flexibility (measured using the fingertip-to-floor test). The treatment program includes 11 exercises that must be administered bilaterally. A mobile app will be developed where each patient will be able to observe the exercises to be carried out. Each session will last 15 minutes with 5 physiotherapy sessions per week for a period of 3 months. It is expected that patients with hemophilia who receive the foam roller intervention will show improvement in mobility, pain, and status of the ankle joint; muscle strength; and function in the lower extremities.

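### The plan names no visit or between-group contrast that decides the primary outcome, and its interaction-then-Bonferroni rule costs power for a posttreatment conclusion

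*Protocol article*

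**What the plan says.** The Abstract (Methods) names the primary outcome: "The primary outcome will be frequency of ankle joint bleeding (self-reported"). It attaches no visit, period or contrast to it.

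Outcome Measures sets two assessments after baseline: "After the treatment period and 3 months after completion, the patients included in both groups (experimental and control) will be re-evaluated". With 3 months of treatment, these fall at about month 3 and month 6.

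Data Analysis gives the decision rule. A repeated measures analysis of variance "will be used to compare the groups (experimental and control) at 3 assessment times (baseline, posttreatment, and follow-up"). Then: "If the interaction is found to be significant, pairwise comparisons will be performed". On error control: "The significance level will be set at α=.05", and "To control the error rate, Bonferroni correction will be applied". The section also opens by listing among its analyses "the changes after the intervention and follow-up period in each group, and the intra and interindividual effect will be analyzed".

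No section says which visit has priority, which pairs are compared or how many comparisons share the .05.

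**The concern.** With two groups and three visits, the interaction has 2 degrees of freedom. It can be significant because of a benefit at posttreatment that later fades, a benefit that appears only after treatment stops, or a worsening in one arm. It does not say which of these happened, so the conclusion passes to pairwise comparisons that the plan leaves open. Six group-by-visit cells give 6 × 5 / 2 = 15 possible pairs. Only some of these are treatment contrasts.

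Two things are at stake. First, the visit that carries the efficacy claim for the primary outcome can be settled after the data are seen. Second, if the claim is meant to rest on the end of treatment, a true effect must pass the interaction test and then a divided significance level, where one prespecified test would do.

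**Working it through.** The article gives no effect size, SD, visit correlation or power figure, so there is no power calculation of its own to reproduce. The check compares the stated route with a single contrast.

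**Inputs from the article.** 70 patients at 1:1, so 35 per arm; α = .05 (two-sided assumed, since sidedness is not stated); three visits; interaction gate; Bonferroni.

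**Assumptions not in the article.** Continuous normal outcome, SD 1, equal correlation ρ of 0.5 or 0.7 between visits. The effect is 0.6 SD at posttreatment and is then sustained, halved or gone at follow-up. Two pairwise comparisons are made, namely the between-group differences in change from baseline at posttreatment and at follow-up, each at .05/2 = .025. This is a lenient reading of the open pairwise family.

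**Step 1: single tests at posttreatment.** Noncentrality is (0.6/s) × √(35/2) = (0.6/s) × 4.183. For a change score s = √(2(1−ρ)); for a baseline-adjusted comparison s = √(1−ρ²). Power is from the noncentral t distribution.

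| | ρ = 0.5 | ρ = 0.7 |
|---|---|---|
| Change score: s, noncentrality | 1.000, 2.51 | 0.775, 3.24 |
| Baseline-adjusted: s, noncentrality | 0.866, 2.90 | 0.714, 3.51 |
| Baseline-adjusted, .05 | 0.81 | 0.93 |
| Change score, .05 | 0.70 | 0.89 |
| Change score, .025 | 0.59 | 0.83 |

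**Step 2: the stated route.** Simulation of the 2 × 3 analysis, 40,000 trials per scenario. The last column is the chance that the interaction is significant at .05 and the posttreatment change contrast is significant at .025.

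| ρ | Effect at follow-up | Gate alone | Gate, then posttreatment contrast |
|---|---|---|---|
| 0.5 | sustained | 0.73 | 0.57 |
| 0.5 | halved | 0.59 | 0.55 |
| 0.5 | gone | 0.73 | 0.57 |
| 0.7 | sustained | 0.93 | 0.82 |
| 0.7 | halved | 0.82 | 0.80 |
| 0.7 | gone | 0.92 | 0.82 |

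**Step 3: where the difference arises.** At ρ = 0.5, using a change score instead of baseline adjustment takes power from 0.81 to 0.70. Halving α takes it from 0.70 to 0.59. The gate takes it from 0.59 to 0.55–0.57. At ρ = 0.7 the same steps run 0.93, 0.89, 0.83 and 0.80–0.82. The gate is the smallest part. For a sustained or fully lost effect, the gate alone (0.73 and 0.92–0.93) is slightly more powerful than the ungated change score (0.70 and 0.89).

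**The case against.** The strongest reply is that a group-by-time analysis with Bonferroni follow-up is a coherent and common frame, and that an analysis plan, which may exist, could name the pairs and the order of visits. That is fair as to the list of pairs. It does not remove the point. The article fixes a rule with an interaction gate, and an analysis plan that named one deciding contrast would replace that rule, not fill it in.

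The power comparison is also partly unequal. It sets a baseline-adjusted test at full α against change scores at half α, and the number of comparisons is assumed. If a significant result at either visit counts as success, the stated route reaches about 0.72 (ρ = 0.5) or 0.92 (ρ = 0.7) for a sustained effect. The loss is therefore specific to a posttreatment conclusion. It cannot be carried over in size to the primary outcome, which is a count of bleeds.

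Three stronger readings are tempting, and the documents do not support them:

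- A reader might infer that within-group improvement shared by both arms would often be reported as efficacy. If both arms change by 0.35 SD with no treatment effect (35 per arm, ρ = 0.5), ungated paired tests single out the experimental arm in about 25% of trials. Under the stated gate this is about 2%. The article also does not say that the pairwise tests include within-group pairs. That is an inference from the opening of Data Analysis.
- A reader might infer that the two visits could contradict each other. Disagreement would mean significance at one visit and not the other. Significant effects in opposite directions occurred in at most 1.5% of simulated trials. If the effect truly fades, a difference between visits is a correct description.
- A reader might infer that the interaction test itself is wasteful. Step 3 shows that this is not generally so.

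Finally, the article gives neither visit priority, so putting posttreatment first is a judgement. It rests on that visit closing the 3-month treatment period.

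**Conclusion.** The point holds in this form: efficacy is decided by an interaction test over three visits followed by unnamed comparisons, and no visit or between-group contrast is designated for the primary outcome. That follows from the text and needs no assumption.

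The size is illustrative. For a continuous outcome with 35 per arm and an assumed 0.6 SD effect, the stated route gives up about 24 to 26 percentage points of power for a posttreatment conclusion at correlation 0.5 (0.81 less 0.55–0.57) and about 11 to 13 at correlation 0.7 (0.93 less 0.80–0.82). These figures rest on normality, on the assumed effect and correlations, and on reading the pairwise family as two change contrasts. Larger families would cost more, but the article does not fix one, so no larger figure is claimed. The change should be made before data are analysed.

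**What to change.** Replace the rule in Data Analysis with the following:

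- One deciding contrast: the between-group difference in ankle bleeding frequency over the 3-month treatment period (posttreatment assessment), adjusted for the baseline value, at two-sided .05, in a model suited to bleeding counts. No interaction test serves as a gate.
- The between-group difference at the 3-month follow-up is tested at .05 only if the first contrast is significant. This fixed sequence keeps the error rate for the two tests at .05 without a Bonferroni split.
- Within-group changes are reported as descriptive and not as evidence of efficacy.

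The cost is a few sentences, with no new visits or patients. The change presupposes a baseline bleeding frequency. The Abstract's statement that data are collected at baseline implies one, although the list of variables in Outcome Measures does not name bleeding. The downside is that an effect appearing only at follow-up could be reported only as exploratory.
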